## Abstract

**Background:**

Psychopathology in women after childbirth represents a significant risk factor for parenting and infant mental health. Regarding child development, these infants are at increased risk for developing unfavorable attachment strategies to their mothers and for subsequent behavioral, emotional and cognitive impairments throughout childhood. To date, the specific efficacy of an early attachment-based parenting group intervention under standard clinical outpatient conditions, and the moderators and mediators that promote attachment security in infants of mentally ill mothers, have been poorly evaluated.

**Methods/Design:**

This randomized controlled clinical trial tests whether promoting attachment security in infancy with the Circle of Security (COS) Intervention will result in a higher rate of securely attached children compared to treatment as usual (TAU). Furthermore, we will determine whether the distributions of securely attached children are moderated or mediated by variations in maternal sensitivity, mentalizing, attachment representations, and psychopathology obtained at baseline and at follow-up. We plan to recruit 80 mother-infant dyads when infants are aged 4-9 months with 40 dyads being randomized to each treatment arm. Infants and mothers will be reassessed when the children are 16-18 months of age. Methodological aspects of the study are systematic recruitment and randomization, explicit inclusion and exclusion criteria, research assessors and coders blinded to treatment allocation, advanced statistical analysis, manualized treatment protocols and assessments of treatment adherence and integrity.

**Discussion:**

The aim of this clinical trial is to determine whether there are specific effects of an attachment-based intervention that promotes attachment security in infants. Additionally, we anticipate being able to utilize data on maternal and child outcome measures to obtain preliminary indications about potential moderators of the intervention and inform hypotheses about which intervention may be most suitable when offered in a clinical psychiatric outpatient context.

**Trial registration:**

Current Controlled Trials
ISRCTN88988596

## Background

Previous research has shown that infants whose mothers suffer from mental disorder are at increased risk for developmental delays, cognitive and functional impairments, physical symptoms and injuries, as well as behavioral and emotional problems in pre-school and school age
[1-6]. Affective and mood disorders, anxiety disorders, posttraumatic stress disorders, obsessive-compulsive disorders, and psychosis with elevated incidences of comorbid diagnoses, varying in onset, course and prognosis, have a higher prevalence in mothers, both postpartum and during early child-age years
[7-17]. In clinical populations, co-occurring personality disorders have to be considered as a crucial part of the global risk that mentally ill mothers experience
[18-21].

The quality of parenting has been viewed as one key mediator of the relationship between maternal psychopathology and the outcome for infants and young children. Maternal psychological and vegetative symptoms, such as social withdrawal, anxiety, emotional lability, impulsivity, and severe exhaustion or weariness, have been found to impinge on the interaction and the development of the relationship between mother and infant. Often, such mothers are emotionally, cognitively and/or behaviorally inhibited or impaired in their ability to recognize and react with appropriate “sensitivity” and “responsiveness”
[22] to their children’s needs. In regard to the infants of these mothers, higher incidences of behaviors, such as persistent crying, motoric restlessness, averted gaze or head position, physical neediness and a lack of expression of delight in the presence of their mothers, have been observed
[23-25]. These behaviors increase the mother’s experience of stress, which further contributes to the maintenance of maladaptive interactional behavioral patterns
[26-32]. Without improvement in these negative interaction cycles, for example, through early interventions, there is a greater likelihood for infants to develop an insecure-avoidant or an insecure-ambivalent or disorganized attachment strategy during the first year of life
[33,34]. According to Ainsworth et al.
[22], in the Strange Situation, insecure-avoidant (Category A) infants do not actively seek proximity and physical contact to their mothers after separation, instead favoring exploration. Insecure-ambivalent (Category C) infants, on the other hand, tend to cling to their caregivers and are characterized by frantic appeals to establish and maintain close proximity to them. At the same time, they show anger and sulky or aggressive behavior towards their mothers. These children are difficult to comfort after separation, that is, they maximize their attachment neediness
[22]. Secure infants (Category B) reach out to their mothers at times of separation distress and calm down easily when comforted so that they can resume play or exploration. If the context of care is additionally characterized by either fear-inducing or frightening parenting practices (e.g., abuse, neglect, aggressive behaviors) or by fearful behaviors on the part of the mother (e.g., signs of anxiety or avoidance, dissociation, etc.), the child is more likely to develop disorganized or disoriented behavioral patterns (Category D)
[35,36]. These include contradictory behavioral tendencies, such as fearful/anxious vacillation between exploring and seeking closeness, temporally uncoordinated or slowed movements and occasional physical or mimic paralysis or “freezing” of the child toward the mother. A maternal mental illness is associated with the development of insecure organized (avoidant, ambivalent) and disorganized attachment styles in the child
[37-41]. Social-emotional maladjustment and related mental health problems in the child are common consequences
[42,43]. Furthermore, mothers with mental disorders themselves are frequently characterized as insecure (dismissing Category Ds or preoccupied Category E), or unresolved (Category U) rather than autonomous (Category F) when attachment representations of their own childhood experiences with attachment figures are assessed
[44-47]. These mothers are troubled by the physical and affective states, needs and behaviors of their infants, which may correspond to “frightening and frightened”
[48] and/or “disrupted”
[49] parenting behaviors
[50].

According to the model of transgenerational transmission
[51], maternal attachment representations influence the child’s attachment more than maternal sensitivity does
[52-54]. Further clinical research on this issue provides evidence that the maternal capacity for mentalization appears to be more crucial than the expressed sensitivity of mothers in the attachment relationship
[55]. The mental abilities of the mother to perceive and recognize her own and the child’s wishes, motives, needs, thoughts and feelings within the context of the attachment relationship and to communicate, as well as to reciprocate these through active engagement, kinesthetic expressions, words and play, represent key competencies for the development of secure attachment, self-regulation and mental health in the child – even if the mother had experienced unprocessed adverse experiences during her own childhood
[56]. Conversely, a diminished capacity to mentalize brought about, for example, by maternal psychopathology, increases the likelihood of the child developing an insecure or disorganized attachment style, unless this process can be changed by an attachment-based intervention.

Research on the treatment of women with postpartum depression has shown that treatment of only the mother (i.e., medication, individual psychotherapy) is not sufficient to buffer against the negative impact of psychopathology on the child’s cognitive and psychosocial development, as well as attachment
[57-61]. Rather, there is a necessity to support mentally ill mothers in their specific needs in caring and relating to their infants. Attachment-based interventions rooted in empirical research on developmental psychopathology are, thus, promising approaches to address these multi-faceted treatment targets. However, to date, very few attachment-based interventions have been systematically tested in formal clinical settings using a randomized controlled trial (RCT) framework involving women with complex postpartum psychiatric disorders.

Attachment-based interventions are designed to promote maternal sensitivity, to change maternal mental representations, to promote attachment security in the child, and/or to support the family, examples include STEEP™
[62]; Wait, Watch, and Wonder
[63]; Circle of Security
[64]; Video Intervention To Promote Positive Parenting
[65]. Each of these interventions has been conducted in different settings (home-based, institutional, individually, group-based), with various at-risk populations (i.e., low SES, depressed mothers, adolescent mothers, preterm infants), and at a wide range of dosages and intensities. Video-analysis is a typical technique implemented as part of these interventions in order to facilitate change. Meta-analytic evidence identifies short-term approaches (< 16 sessions), targeting maternal sensitivity as being the most effective, and sensitivity-focused interventions conducted with clinically referred samples (i.e., *DSM-III-R* depressed mothers), as being more effective than interventions with other groups
[66]. Attachment security, in particular, has been found to be readily influenced by sensitivity-focused interventions
[66]. Yet, it remains unknown how brief attachment-focused interventions designed for at-risk populations differentially impact mothers’ mentalizing, mental representations of attachment, beyond sensitivity and mental illness, and children’s level of attachment security.

The Circle of Security intervention is a brief, behavioral and insight-oriented therapeutic group approach for promoting attachment and autonomy in the parent–child relationship. It combines psycho-educational, cognitive-behavioral, and psychodynamic understanding and intervention techniques. Given that women with various and co-occurring mental illnesses after childbirth differ greatly in their requirements, openness and motivation for, and compliance with mother-infant treatment, the COS intervention can allow individualized, flexible and deepened therapeutic access to each mother-infant dyad, which is further supported by its group character. Therefore, within our clinical context, COS seems to be a promising intervention to detect and treat early difficulties in the development of secure attachment relationships.

The current RCT is designed to evaluate the efficacy of the COS intervention for mentally ill mothers with infants, for the first time in Germany and in a clinical context. The main research question is whether COS, in comparison with treatment as usual (TAU), increases attachment security and prevents the development of insecure and/or disorganized attachment by promoting maternal sensitivity and mentalizing measured after treatment at follow-up when the children are aged 16–18 months. We hypothesize that following treatment there will be a higher proportion of secure child–mother attachment in the COS arm compared to TAU. This paper describes the design of the trial, the implementation of the study protocol in a child and adolescent psychiatric outpatient unit, and the data analysis strategies.

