#### Secondary outcomes

**Mini-MBQS** - Maternal sensitivity. The revised mini-Maternal Behavior Q-Sort (mini-MBQS) for video coding
[73], a 25-item observational coding instrument, is used for measuring the quality of maternal sensitive behavior. The q-set items relevant to attachment are mapped onto a prototypically sensitive mother
[74]. During the mini-MBQS sorting process, coders systematically evaluate and sort each of the 25 q-set items into one of the five categories (i.e., “most like mom”, “like mom”, “unlike mom”, “neither like nor unlike mom, “least like mom”) respectively, based upon behavioral observations of videotaped interactions between mother and child. Correlation scores are calculated, varying from -1.0 (least sensitive or responsive) to 1.0 (prototypically sensitive or responsive) between the observer sorts and a criterion sort for the prototypically sensitive and responsive mother, which is provided by the developers of the instrument. In this trial, mini-MBQS data are derived from videotaped 5-minute free play and 5-minute book reading interactions at baseline and follow-up, each coded by two independent raters blind to treatment allocation.

**DIP** - The Disconnected and extremely Insensitive Parenting rating procedure
[75] is used to identify extreme insensitivity and/or disconnection in the mother. The DIP captures those maternal behaviors that are most likely related to poor child attachment outcomes
[75]. Disconnected behavior and extreme insensitivity are rated on a scale ranging from 1 to 9, indicating an incrementally increasing display and/or prolonged duration of such behaviors. For pre- and post-assessment, the DIP is administered for the same 5-minute-interaction episodes (free play, book reading) as the mini-MBQS by two independent raters who each have undergone DIP rating and reliability procedure training.

**AAI** - The Adult Attachment Interview and its respective scoring and classification system
[70,76] represent the “gold standard” for classifying maternal state of mind with regard to attachment (as F, Ds, E, U). In the current trial, it is administered at baseline and follow-up. Mothers classified as unresolved (U) with regard to loss or trauma will also be assigned into a secondary best-fitting organized attachment category. The interviews will be transcribed verbatim and coded by two reliable raters who are blind to treatment allocation.

**RF -** The Reflective Functioning (RF) scale of the AAI

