#### Randomization procedures and methods to minimize bias

Eligible patients were randomly assigned to the COS intervention or TAU in a ratio of 1:1. An electronic randomization list was generated using Randlist 1.2 as a random generator. Unique randomization numbers were generated to ensure that the study arm assignment was unbiased. Randomization was stratified for two infant age groups (4–6 months vs. 7–9 months) and separate random lists were created for each age group. Block sizes of six to eight were used for the randomization of the treatment arms. The randomization list was generated by the randomization representative and was stored in a password-protected electronic document accessible only by the randomization representative. Each random number was stored in a concealed randomization envelope. After a patient’s eligibility for the study was determined, the next available randomization number was assigned to the patient, in ascending order. To minimize bias that could have arisen from knowledge of treatment allocation, all outcome assessors were blind to treatment allocation and a random sample of outcome measures was re-rated by independent assessors.

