### Statistical methods

#### Sample size and power

The primary outcome for treatment efficacy is the rating of quality of child attachment at follow-up at children’s age 16–18 months (COS vs. TAU) by an objective rater blind to treatment allocation. Differences in distributions of the quality of child attachment (secure vs. insecure-avoidant, -resistant, -disorganized) between both treatment modalities are calculated by a chi-square test of significant statistical independence. A power analysis for comparing COS and TAU with a power of 80% and the probability of making a Type I (α) error of 5%, with a medium effect (*W* = 0.3) suggested a recruited sample size of N = 80.

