### Primary outcome

For the primary outcome, that is, child attachment security (vs. insecurity) as a categorical variable, differences of the proportions of child attachment security between TAU and COS treatment arms will be estimated by a chi-square test of statistical significance.

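### The primary chi-square makes no use of the mother's pre-randomisation attachment class; the test is valid, but stratifying on that class would probably recover a few points of power at almost no cost

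*Protocol article*

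**What the plan says.** All references are to the protocol article.

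- **Primary analysis.** Under Statistical methods, Primary outcome: "differences of the proportions of child attachment security between TAU and COS treatment arms will be estimated by a chi-square test of statistical significance". No covariate or stratum is named there or under Sample size and power.
- **Prognostic ranking.** The Background, citing a model of transgenerational transmission, says that "maternal attachment representations influence the child’s attachment more than maternal sensitivity does".
- **Measurement.** Of the AAI, the Secondary outcomes section says: "In the current trial, it is administered at baseline and follow-up"; Table 1 agrees. Recruitment and baseline procedures places the whole baseline assessment before random allocation.
- **Randomisation.** "Randomization was stratified for two infant age groups (4–6 months vs. 7–9 months"), and by nothing else.
- **Other models.** Item h, the logistic model of child attachment, has treatment, sensitivity, reflective functioning, BDI, SCL-90 and PSI, but not the AAI. In the listed analyses the AAI appears only as change over time: as outcome in item d, and as a predictor in item g, whose outcome is not named.
- **Moderation and mediation.** The Abstract (Methods/Design) names attachment representations, at baseline and follow-up, among the possible moderators or mediators of child attachment security.

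**The concern.** A baseline variable that predicts the outcome and is already being collected can sharpen the treatment comparison if the analysis conditions on it. Here the article names such a variable, measures it before allocation, and then fixes a primary test that cannot use it. Item h even adjusts for sensitivity, which the Background ranks lower, and leaves the AAI out.

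What is at stake is power and precision. At the sample size actually set, power under the article's own effect size is already below 80%, so a few points matter. Prespecifying the adjustment also avoids a later argument about whether to adjust if autonomous mothers turn out to be unevenly split between the arms.

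**Working it through.** **1. The article's own figure.** Noncentral chi-square, 1 degree of freedom, two-sided 5%, noncentrality = N × W².

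- N = 80: 80 × 0.09 = 7.20, power 76.5%.
- N = 88: 88 × 0.09 = 7.92, power 80%.
- N = 72, the number set in Limitations: 72 × 0.09 = 6.48, power 72.1%.

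So the statement that the power analysis "suggested a recruited sample size of N = 80" does not reproduce. That is a separate matter; it is given here only to fix the starting power.

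**2. Inputs for the comparison.**

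- From the article: 36 per arm, 1:1 allocation, 5% level, W = 0.3.
- Assumed security rates, because the article gives none: 35% vs 65%, where W = (0.30/2)/√(0.50 × 0.50) = 0.30; and 30% vs 60%, where W = 0.15/√(0.45 × 0.55) ≈ 0.30.
- Assumed, because the article gives neither: 20-40% of mothers autonomous (F) at baseline, and a within-arm gap in child security between autonomous and other mothers of 0 to 40 points.
- No drop-out and no missing AAI, except where stated.
- A 50-point gap with 20% autonomous and 65% secure is impossible, since 0.65 + 0.50 × 0.80 = 1.05. The range therefore stops at 40.

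**3. Simulation.** 40,000 trials per setting; uncorrected Pearson chi-square against CMH stratified by baseline AAI (F vs Ds/E/U).

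| Gap in child security | Crude power | CMH power |
|---|---|---|
| 0 points | 72-73% | 72-73% |
| 20 points, both arms | 72-73% | 74-75% |
| 30 points, both arms | 72-73% | 75-77% |
| 40 points, both arms | 72-73% | 78-81% |
| 40 points in TAU, none in COS | about 72% | about 74-75% |

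The type I error of CMH is 4.8-5.1%. With 30 per arm, that is (36 − 30)/36 = 17% lost, and a non-prognostic AAI, CMH can be about 1 point worse than the crude test.

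**4. Check by hand (35% vs 65%, 30% autonomous).** The share of within-arm variance that the AAI explains is gap² × 0.3 × 0.7 / (0.35 × 0.65). Dividing 6.48 by one minus that share gives the new noncentrality λ, and power ≈ Φ(√λ − 1.96).

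- 20 points: 0.0084/0.2275 = 3.7%; λ = 6.73; power 74%.
- 30 points: 0.0189/0.2275 = 8.3%; λ = 7.07; power 76%.
- 40 points: 0.0336/0.2275 = 14.8%; λ = 7.60; power 79%.

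These agree with the simulation.

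**5. Second parameterisation.** With an AAI-to-security odds ratio, 35% vs 65%, 20-50% autonomous and 36 per arm, CMH gives 74% at OR 2, 75-77% at OR 4 and 78-83% at OR 8, against 72-73% crude (4,000 runs per setting). The pattern is the same: little if the association is weak, useful if it is strong.

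**6. Chance imbalance.** About 1 trial in 20 has a between-arm difference of 19-22 points or more in the share of autonomous mothers. At a 40-point gap that moves the crude difference by 0.40 × 0.19 to 0.40 × 0.22, about 8-9 points. The crude 95% interval is already 1.96 × √(2 × 0.35 × 0.65/36) = ±22 points, and that width includes such variation.

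**The case against.** The strongest reply is that nothing here is an error. Under 1:1 randomisation the unadjusted chi-square has the right type I error, and chance imbalance on the AAI is part of its standard error. That stands. A reader might infer from step 6 that the crude comparison is biased, or that imbalance goes unaccounted for; the design does not support that.

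Second, the gain rests on figures that the article does not contain. The Background gives only a ranking against sensitivity, attributed to a model, and it goes on to place mentalising above sensitivity too. A reader might infer that the AAI is the strongest predictor of child attachment, or that the gain is assured; neither follows. If COS weakens the link between the mother's baseline class and the child's attachment, as its rationale suggests, the gain shrinks to 2-3 points.

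Third, it goes too far to say that the trial ignores baseline attachment representations, because the Abstract plans to examine them as a moderator or mediator. That is a different purpose, however, and does not adjust the primary comparison.

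Fourth, there are practical limits. The AAI has to be transcribed and coded, so classes may not have been known at allocation, and the six COS groups are described as already realised. The choice of stratification factor is therefore not something to reopen. At 20% autonomous, that stratum holds only about 0.20 × 72 = 14 dyads.

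Finally, a chi-square yields no estimate or interval, although the article says that it will estimate the difference. Interval reporting may well be covered in an analysis plan that is not shown, so no separate weight is put on this.

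**Conclusion.** The point holds as one of efficiency. The article fixes an unadjusted primary test while collecting, before allocation, a variable that it regards as influential for the same outcome. The test is valid and its result would not be biased. Under the stated assumptions, stratifying on baseline AAI class adds about 2 points of power at a 20-point gap and about 6-8 at 40, 2-3 if a 40-point gap is confined to TAU, and none at zero, with a possible loss of about 1 point under heavy drop-out and a non-prognostic AAI. The association and the share of autonomous mothers are assumptions throughout. The change is worth making because it costs almost nothing and the trial starts from about 72% power.

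**What to change.** Before the attachment codes are linked to treatment arm:

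- Make the primary analysis a CMH test of secure versus insecure by arm, stratified by baseline maternal AAI class, in two levels: autonomous (F) versus Ds, E or U. Four classes would be sparse at N = 72.
- Use the baseline value only. The follow-up AAI and the change in AAI are post-treatment.
- Report the Mantel-Haenszel risk difference with its 95% confidence interval as the primary estimate.
- Keep the crude chi-square as a supportive analysis.
- State in advance how mothers without a codable baseline AAI are handled, for example as a separate stratum.

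The cost is a paragraph of analysis wording. It needs no new data or participants. The downside is that baseline AAI coding must be complete before the primary analysis.

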### Assessment and outcomes measures

All measures of pre- and post-assessment are listed in Table 
1.

**Table 1 T1:** Assessments administered at baseline and follow-up throughout the trial

**Time point**	**SSP**	**MBQ-S**	**DIP**	**AAI**	**AAI-RF**	**PRFQ-1**	**SCID-I,-II**	**BDI**	**SCL-90**	**PSI**	**DERS**	**CBCL**	**FBB-E**

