**Follow-up**													
Child age 16–18 months	√	√	√	√	√	√	**-**	√	√	√	√	√	√

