[77] is utilized to measure maternal mentalizing, which is defined as the capacity of the mother to reflect upon her own self and close others in terms of intentional mental states. The RF allows for overall ratings of reflective functioning on a nine-point scale ranging from 1 (lacking RF) to 9 (exceptional RF), with two additional RF scores indexing the absence of mentalizing, that is, -1 (negative RF), 0 (lacking RF). RF-ratings will be performed on the AAI obtained at baseline and follow-up by two independent raters blind to treatment allocation.

**PRFQ-1 –** The Parental Reflective Functioning Questionnaire-1
[78] is used as an alternative instrument for assessing RF via self-report. The PRFQ-1 assesses the levels of parental mentalization up to the child’s age of 3 years. It consists of 39 items comprising three subscales prototypically describing high, low, and neither high nor low mentalizing in mothers and fathers. Scoring procedures precepts yield a total score on all three subscales. PRFQ-1 is administered at baseline and follow-up.

**SCID-I** – The German version of the Structured Clinical Interview
[79] for DSM-IV
[80] axis I disorders is used to verify clinical DSM-IV-Axis-I diagnoses. SCID-I interviews were conducted by trained researches at baseline.

**SCID-II** – The German version of the Structured Clinical Interview (SCID-II) for personality disorders is used to identify mothers with probable DSM-IV-Axis II personality disorders. SCID-II interviews were conducted by trained researchers at baseline.

**BDI** – The Beck Depression Inventory
[81,82] is administered to screen for depressive symptoms in the mothers at baseline and follow-up. It consists of 21 items, scaled from zero to three, which are summed to a global score, indicating clinical significance of self-reported depressive symptoms.

**SCL-90-R** – The revised Symptom Checklist by Derogatis
[83] (German version:
[84]) is used to assess maternal psychopathological symptoms. The Global Severity Index, as a sum score of the SCL-90-R, is applied to determine maternal psychopathology at baseline and follow-up.

**PSI** – The Parenting Stress Index
[85] (German:

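### Mediation is a stated aim, but the maternal variables are measured after treatment only in the follow-up assessment that yields the outcome, so their order cannot be established

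*Protocol article*

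**What the plan says.** Two places make mechanism part of what the trial will show. The Abstract (Methods/Design) says the investigators will determine whether the distribution of secure children is "moderated or mediated by variations in maternal sensitivity, mentalizing, attachment representations, and psychopathology obtained at baseline and at follow-up". The closing paragraph of the Background asks, as the main research question, whether COS "increases attachment security and prevents the development of insecure and/or disorganized attachment by promoting maternal sensitivity and mentalizing measured after treatment at follow-up".

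The schedule is in Table 1, titled "Assessments administered at baseline and follow-up throughout the trial". It has a baseline row (child age 4–9 months) and one follow-up row, "Child age 16–18 months". The Strange Situation is marked at follow-up only, and the sample-size section defines the primary outcome as the "rating of quality of child attachment at follow-up".

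The measure descriptions agree with the table. For sensitivity, "mini-MBQS data are derived from videotaped 5-minute free play and 5-minute book reading interactions at baseline and follow-up". For mentalizing, "RF-ratings will be performed on the AAI obtained at baseline and follow-up by two independent raters blind to treatment allocation". The PRFQ-1, AAI, DIP, BDI and SCL-90 are also scheduled at baseline and follow-up.

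Under the analysis of secondary outcomes, item g uses pre-post changes in sensitivity, mentalizing and attachment representations as predictors, without naming the dependent variable. Item h regresses attachment security on treatment, sensitivity, RF, symptoms and parenting stress, without saying from which time point the predictors come.

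**The concern.** A mediator has to change after treatment begins and before the outcome is settled. Here the baseline values precede treatment, and the only later values are taken in the same follow-up as the outcome. Attachment has no earlier measurement.

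Two accounts then lead to the same kind of data. In one, COS raises sensitivity, which makes the child secure. In the other, COS makes the child secure by some other route, and a secure child is easier to play and read with, so the mother is coded as more sensitive. The protocol's own theory allows the second account: the Background describes infant behaviour that adds to the mother's stress and sustains poor interaction patterns.

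At stake is the interpretation of items g and h. An association between follow-up sensitivity and security, read alongside the Abstract and Background, could be taken as the mechanism of COS when it may be partly a consequence of attachment.

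**Working it through.** The plan gives no figure on this point to reproduce. The check sets the schedule against the aim, then illustrates the consequence.

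**Step 1: timing of each measure (Table 1 and the measure descriptions).**

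| Variable | Before treatment | After treatment, before follow-up | Follow-up, 16–18 months |
|---|---|---|---|
| Sensitivity (MBQS, DIP) | yes | none | yes |
| Mentalizing (AAI-RF, PRFQ-1) | yes | none | yes |
| Attachment representations (AAI) | yes | none | yes |
| Symptoms (BDI, SCL-90) | yes | none | yes |
| Child attachment (SSP) | no | none | yes |

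The third column is empty for all four domains named in the Abstract. The primary hypothesis speaks of attachment both after treatment and at follow-up, but Table 1 contains no separate end-of-treatment assessment.

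**Step 2: the interval without measurement.** COS has 20 weekly sessions. 20 weeks ÷ (52/12 weeks per month) ≈ 4.6 months. Assuming no wait for a group to fill, COS ends at age 4 + 4.6 = 8.6 to 9 + 4.6 = 13.6 months. Follow-up is then 16 − 13.6 = 2.4 to 18 − 8.6 = 9.4 months later. The actual wait is not given and would shorten this. The Background places the formation of insecure or disorganized strategies in the first year of life, so the maternal variables are next measured at least 16 − 12 = 4 months after the end of that period.

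**Step 3: what a mediation test does when there is no mediation.** The following inputs are assumptions, not figures from the documents:

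- Security 35% under TAU and 65% under COS. With equal arms this matches the planned W: (0.65 − 0.35) / (2 × √(0.5 × 0.5)) = 0.30.
- Follow-up sensitivity = 0.5 × baseline sensitivity + d × security + error, with baseline variance 1, error variance 1 − 0.5² = 0.75, and d = 0.5 or 0.8. Sensitivity has no effect on security.
- Fitted models: linear regression of follow-up sensitivity on arm and baseline sensitivity; logistic regression of security on arm, follow-up and baseline sensitivity. Mediation is declared when both path coefficients have z > 1.96.

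Both paths are non-zero by construction. The arm-to-sensitivity path is 0.30 × d = 0.15 or 0.24. The sensitivity-to-security log odds ratio is d / 0.75 = 0.67 or 1.07. The simulated medians at N = 2000 were 0.15 and 0.24, and 0.66 and 1.07.

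| N | False mediation, d = 0.5 | False mediation, d = 0.8 |
|---|---|---|
| 72 | 5.9% | 16.7% |
| 80 | 7.5% | 19.8% |
| 400 | 39.6% | 70.8% |
| 2000 | 96.0% | 100% |

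The rates at 72 and 80 bear on this trial. The larger sizes show only that the problem is one of identification: neither more data nor baseline adjustment removes it. One limit of the illustration is that the arm coefficient did not shrink when follow-up sensitivity was added (medians at N = 2000, d = 0.5: 1.24 without and 1.24 with). A rule requiring shrinkage would behave differently; the pattern is that of partial mediation with a remaining direct effect.

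**The case against.** The strongest reply is that the trial's confirmatory claims do not depend on mediation, and this stands. The Aims and hypothesis section states one primary hypothesis on the proportion secure and three secondary hypotheses on COS-versus-TAU effects on maternal variables. The sample-size and primary-outcome sections size and test only the arm difference in security. No indirect-effect test is listed, and the Abstract's Discussion promises only preliminary indications about moderators. A reader might infer that the plan commits to a confirmatory mediation test, or that the primary result is compromised. The documents support neither.

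Three further stronger readings also fail:

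- A reader might take Table 1 to mean that all measures are made at one visit. It gives a follow-up window of 16–18 months and states no order within it; baseline took several sessions, and follow-up may too. An order within the window would help only partly, because attachment forms earlier.
- A reader might think the reverse path equally plausible for every proposed mediator. It is most plausible for observed play and book reading. RF and state of mind are scored from an interview about the mother's own childhood attachment, so an effect of infant security on them is less direct. Parenting stress (PSI) is not among the four mediators the Abstract names.
- A reader might conclude that no mediation model can be fitted. One can be, under stated assumptions about direction and mediator-outcome confounding. The schedule prevents the direction from being tested.

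It can also be said that the Background's clause merely describes what COS targets. That is possible, but the Abstract's statement about mediation does not allow that reading, and the Limitations do not mention timing.

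**Conclusion.** The point holds as a mismatch between two statements of aim and the assessment schedule. The schedule cannot establish that change in sensitivity, mentalizing, attachment representations or symptoms preceded attachment security, because no post-treatment value is scheduled before the follow-up that yields the only Strange Situation. This rests on Table 1 and the measure descriptions alone, and a later analysis plan cannot supply a missing measurement.

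The practical size is moderate. The false-mediation rates of roughly 6–20% at N = 72 to 80 depend on an assumed reverse effect of 0.5 to 0.8 SD and on one particular test, so they are illustrative. The randomized comparisons of COS with TAU on security, sensitivity and mentalizing stand as planned, as do moderator analyses using baseline values. What changes is what the trial may conclude about how COS works.

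**What to change.** - Reword the Abstract (Methods/Design) and the main research question in the Background to agree with the Aims and hypothesis section: the confirmatory question is the arm difference in attachment security at 16–18 months.
- State that moderator analyses use baseline values.
- For item g where attachment is the outcome, and for item h, state that models using follow-up or change scores are exploratory concurrent associations that do not establish mechanism. If a mediation estimate is reported, give its assumptions on direction and on no mediator-outcome confounding beside it. The word mediation need not be banned.
- Add the missing time order to the Limitations.

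The cost is wording. The trial gives up a firm mechanism claim. No new visit or measurement is needed, and the primary analysis is unchanged.
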